## Abstract

**Introduction:**

Chest pain is a common reason for consultation in primary care. To rule out acute coronary syndrome (ACS), general practitioners (GP) refer 40%–70% of patients with chest pain to the emergency department (ED). Only 10%–20% of those referred, are diagnosed with ACS. A clinical decision rule, including a high-sensitive cardiac troponin-I point-of-care test (hs-cTnI-POCT), may safely rule out ACS in primary care. Being able to safely rule out ACS at the GP level reduces referrals and thereby alleviates the burden on the ED. Moreover, prompt feedback to the patients may reduce anxiety and stress.

**Methods and analysis:**

The POB HELP study is a clustered randomised controlled diagnostic trial investigating the (cost-)effectiveness and diagnostic accuracy of a primary care decision rule for acute chest pain, consisting of the Marburg Heart Score combined with a hs-cTnI-POCT (limit of detection 1.6 ng/L, 99th percentile 23 ng/L, cut-off value between negative and positive used in this study 3.8 ng/L). General practices are 2:1 randomised to the intervention group (clinical decision rule) or control group (regular care). In total 1500 patients with acute chest pain are planned to be included by GPs in three regions in The Netherlands. Primary endpoints are the number of hospital referrals and the diagnostic accuracy of the decision rule 24 hours, 6 weeks and 6 months after inclusion.

**Ethics and dissemination:**

The medical ethics committee Leiden-Den Haag-Delft (the Netherlands) has approved this trial. Written informed consent will be obtained from all participating patients. The results of this trial will be disseminated in one main paper and additional papers on secondary endpoints and subgroup analyses.

**Trial registration numbers:**

NL9525 and NCT05827237.

Strengths and limitations of this studyThe study design is a randomised controlled diagnostic trial, which prospectively evaluates a clinical decision rule, including a high-sensitive cardiac troponin I (hs-cTnI) point-of-care test, to rule out acute coronary syndrome (ACS) in primary care.The study includes a cost-effectiveness analysis, to evaluate the efficiency of the clinical decision rule and the impact on the healthcare system.The Atellica VTLi hs-cTnI analyser provides reliable hs-cTnI measurements within only 8 min in capillary blood obtained by a fingerstick.Inclusion is based on clinical suspicion of ACS by general practitioners, which reflects daily clinical practice, but may lead to inclusion bias.Patients with an onset of chest pain <1 hour are excluded, because hs-cTnI measurement within this time window may be false negative due to time-dependent troponin release.

## Introduction

Chest pain is a common reason for consultation in primary care.^1 2^ In 4%–7% of patients presenting with chest pain, the pain is caused by acute coronary syndrome (ACS).^1–3^ Early identification and treatment of patients with ACS are important to avoid cardiac morbidity and mortality.^4^ However, it is challenging for general practitioners (GPs) to distinguish ACS from other—less acute and life-threatening—causes of chest pain, as they have to rely on symptoms and clinical signs only.^5^ Consequently, GPs refer approximately 40%–70% of patients presenting with chest pain to the hospital for further examination.^1 6^

Following referral, only 10%–20% of the patients are diagnosed with ACS.^7–9^ The relatively high number of referrals puts a high burden on patients and may lead to potentially avoidable adverse patient outcomes due to the risks associated with (unnecessary) diagnostic tests and overcrowding of emergency departments (ED).^10–12^ In addition, a high referral rate puts a lot of pressure on the healthcare system. Finally, evaluation of patients in the ED is costly, which has a significant impact on society as well.^13^ Therefore, measures to improve the referral efficiency of patients with acute chest pain are crucial.

A clinical decision rule may help GPs to safely rule out ACS and reduce hospital referrals. Previous studies in ED settings showed that a single high-sensitive cardiac troponin-I (hs-cTnI) measurement with or without a risk score is safe and effective to rule out ACS.^7 9 14^ However, due to the low incidence of ACS in primary care, results from ED settings are not generalisable to primary care settings. Although use of a troponin point of care test (POCT) in primary care reduced the number of referrals in both a model-based and an observational study, the impact has yet to be studied in clinical practice.^15–17^

Therefore, this clustered randomised controlled trial (RCT) aims to evaluate the impact of a primary care decision rule for acute chest pain, consisting of a risk stratification score combined with a hs-cTnI-POCT on the number of hospital referrals, and to assess its diagnostic accuracy. In addition, secondary endpoints including cost-effectiveness will be assessed.

## Methods and analysis

### Study design

The POB HELP study is a clustered diagnostic RCT. The study will be conducted in general practices in three regions in the Netherlands (Leiden, Maastricht and Venlo). General practices will be randomised to the intervention or control group in a 2:1 ratio. Randomisation is stratified for the three regions to ensure even distribution of rural and urban areas. Randomisation is done by Castor Electronic Data Capture using a variable block randomisation method.^18^ Patient inclusion started on 18 August 2021 and the study is planned to end on 1 July 2024.

### Study population

Patients visiting their GP, or visited by their GP, for acute chest pain symptoms in which the GP suspects an ACS, are eligible for inclusion. Patients who contact their GP by telephone with acute chest pain highly suspicious for ACS are not eligible for inclusion. For these patients, an ambulance is sent directly to the home address by the doctor’s assistant, in accordance with usual care. Exclusion criteria are: age <18 years, trauma preceding the pain, inability to speak Dutch or understand the informed consent form, onset of chest pain within less than 1 hour and haemodynamic instability (table 1). Patients who match the eligibility criteria and provide informed consent are included in the study.

**Table 1 T1:** Inclusion and exclusion criteria

Inclusion	Exclusion
≥18 years of age	<1 hour since onset of symptoms
Acute chest pain	Inability to speak or understand Dutch
Seen by the general practitioner	Haemodynamic instability
	Trauma preceding chest pain

### Regular care

In general practices randomised to the control group, included patients will receive standard care in accordance with the Dutch GP guideline for ACS.^19^ Standard care consists of a medical history and physical examination by the GP. In addition, an ECG can be performed, however, an ECG device is not available in many general practices in the Netherlands. Based on this information, the GP will decide to either reassure the patient (‘watchful waiting’), consult a cardiologist or refer the patient to the hospital. The GP is responsible for the follow-up of the patient.

### Intervention

For patients included in general practices randomised to the intervention group, the GP will apply a clinical decision rule consisting of the Marburg Heart Score (MHS) and a hs-cTnI-POCT (figure 1).^3 20 21^

**Figure 1 F1:**
[figure not shown]
Flow chart of the clinical decision rule.

The MHS consists of a five-item score and each positive item results in 1 point: (1) age and sex (male ≥55 years, female ≥65 years), (2) history of cardiovascular disease (ie, stable coronary artery disease, prior myocardial infarction, coronary intervention, ischaemic cerebrovascular accident or peripheral atherosclerosis), (3) patient assumes a cardiac origin of the chest pain, (4) pain worsening with exercise and (5) pain not reproducible with palpation. The ACS risk is considered low for patients with an MHS of ≤2 points and high for patients with ≥3 points.^3 20^

The hs-cTnI measurement is performed using the Siemens Atellica VTLi immunoassay analyser.^21^ The analyser is easy to use and guides the user step by step through the process. Prior to the start of the study, the staff, including the doctor’s assistants and at least one GP per general practice, is trained by a study employee. A study employee is available during office hours to provide assistance by telephone when necessary. Blood is obtained by a fingerstick, which makes it highly suitable for a prehospital setting. The droplet of blood is applied to a cartridge using a capillary transfer device. The turn-around time from the application of the droplet of blood to the test result is approximately 8 min. The limit of detection is 1.6 ng/L and the limit of quantitation is 8.9 ng/L (at 10% CV) and 3.7 ng/L (at 20% CV).^22^ The 99th percentile overall, for men and for women are, respectively, 23, 27 and 18 ng/L. A hs-cTnI level ≤3.8 ng/L is considered very low and is used as a cut-off in this study to exclude ACS.^23^

The combination of the MHS and the hs-cTnI-POCT measurement results in three possible recommendations (figure 1):

MHS ≤2 points and hs-cTnI-POCT ≤3.8 ng/L: ACS is safely excluded and watchful waiting is recommended.either MHS ≤2 points and hs-cTnI-POCT ≥3.9 ng/L or MHS ≥3 and hs-cTnI-POCT ≤3.8 ng/L: ACS cannot be excluded, consultation with a cardiologist is recommended.MHS ≥3 and hs-cTnI-POCT ≥ 3.9 ng/L: The risk for ACS is increased and direct referral to the ED is warranted.

If the GP or consulting cardiologist disagrees with the recommendation provided by the clinical decision rule, they are allowed to overrule it. The GP is responsible for the patient’s follow-up, in line with regular care.

In previous studies, the MHS showed good diagnostic accuracy in ruling out stable coronary artery disease in primary care, but was insufficient to rule out ACS safely.^3 8 20 24^ We hypothesise that adding the hs-cTnI-POCT to the MHS will result in a safe and accurate clinical decision rule to rule out ACS in primary care. Even though the aim of the clinical decision rule is to rule out ACS in patients with acute chest pain, it may also reduce missed ACS diagnosis in patients presenting with atypical symptoms.

An ECG is not included in the decision rule, as an ECG device is not available in all general practices in The Netherlands. Nonetheless, GPs with an ECG device available are free to make an ECG and overrule the recommendations of the clinical decision rule as they deem necessary. However, it is important to notice that an ECG may be normal in 30% of patients presenting with non-ST elevated myocardial infarction and is, therefore, unsuitable for excluding ACS safely.^25^

### Safety

Following ESC guidelines the minimum time since onset of chest pain in this study is 1 hour.^25^ Approximately 10% of all patients with acute chest pain in primary care present within 1 hour since onset of symptoms.^8 26^ Due to the time-depended release of troponin, the decision rule is not applicable for these very early presenters.^25^ Hs-cTnI measurements within this time window may give false negative results, and therefore, wrongfully rule out ACS. Previous studies including early presenters (<3 hours since onset of symptoms), showed decreased sensitivity in patients presenting <1 hour since onset of chest pain.^16 25–28^ In patients presenting 1–3 hours since onset of chest pain, study results are still inconclusive, but using a hs-cTnI—with a cut-off value around the limit of detection, rather than below the 99th percentile—seems safe in combination with clinical evaluation and is recommended in the ESC guideline.^25 29 30^ To ensure safety and minimise the risk of wrongfully excluding ACS, we took the following additional actions. First, patients contacting their GP by telephone with symptoms highly suspicious for ACS are not eligible for inclusion and an ambulance is sent to their home immediately. Patients who are haemodynamically unstable when seen by their GP are excluded as well and require immediate referral. Second, the hs-cTnI is embedded in a clinical decision rule, so patients with typical symptoms will be discussed with a cardiologist, even when hs-cTnI measurement is very low. Third, GPs are instructed that the recommendation of the clinical decision rule may be over-ruled when deemed necessary by the GP or consulting cardiologist. Lastly, a data safety monitoring board (DSMB) is installed to evaluate the safety of the study after 100, 500 and 1000 inclusions.

### Primary endpoints

The study has two primary endpoints. The first primary endpoint is the hospital referral rate for acute chest pain within 24 hours and 6 weeks after inclusion. The second primary endpoint is the diagnostic accuracy of the clinical decision rule. To study the diagnostic accuracy (ie, sensitivity, negative predictive value), the incidence of ACS and major adverse cardiac events (MACE) at the index consultation, within 6 weeks and 6 months after inclusion will be assessed. MACE is defined as a combined endpoint of ACS, percutaneous coronary intervention, coronary artery bypass grafting, coronary angiography revealing procedurally correctable stenosis managed conservatively and all-cause mortality.^7 31 32^

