### Final diagnosis

The final diagnosis will be made based on GP’s medical records, including all letters from hospitals. All cases will be reviewed by an independent endpoint committee consisting of a cardiologist and GP for adjudication of the final diagnosis and the occurrence of MACE. The committee will be blinded for the randomisation and hs-cTnI on presentation. In case of disagreement, a second cardiologist will be consulted. The final diagnosis will be classified as ACS, stable coronary artery disease, cardiac but non-coronary disease, non-cardiac chest pain or death. ACS comprises myocardial infarction (ST-segment elevation myocardial infarction (STEMI) and non-STEMI (NSTEMI)) and unstable angina pectoris. Myocardial infarction is defined conform the fourth universal definition of myocardial infarction.^33^

A coronary angiogram (CAG) is the golden standard to establish the presence of coronary artery disease. However, CAG is costly and not without risk (eg, bleeding in approximately 7% and procedure-related myocardial infarction in approximately 6% of patients undergoing CAG).^34 35^ Therefore, we consider it too invasive and essentially unethical to perform a CAG in each patient in this relatively low-risk population. Hence, we will use a delayed reference standard, defined as ACS and MACE at the index consultation, within 6 weeks and 6 months after inclusion, to determine the diagnostic accuracy of the decision rule. The delayed reference method has been reported as a valid alternative if a golden standard test is too invasive and the disease is not self-limiting.^36^ This method has been used in similar studies before.^7 20 32 37^

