### Sample size calculation

In primary care in the Netherlands, the reported hospital referral rate of patients with chest pain ranges from approximately 40%–70%.^1 6^ Similarly, a Swiss and Swedish study found referral and diagnostic testing rates of 59% and 43%, respectively.^44 45^ Based on these referral rates, we conservatively assumed a hospital referral rate of 40%. For the primary endpoint, we estimated a 10% decrease in referrals, resulting in 30% referrals, which is in line with a previous study estimating a 10% decrease in referrals when using the MHS.^45 46^ Group sample sizes of 448 (control group) and 896 (intervention group) achieve 80% power to detect the difference of 10% between both groups with a significance level (alpha) of 0.05 using a two-sided Z-test.^47^ The sample size is adjusted for a clustering effect with an intraclass correlation coefficient of 0.05 and for 1:2 randomisation.^48^ The estimated sample size needed is 500 for the control group and 1000 for the intervention group, accounting for a 10% lost to follow-up.

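### Hospital referral is primary at two time windows with no lead, order or combination rule, while the sample size covers one unnamed comparison; accuracy likewise has no lead target

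*Protocol article*

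**What the plan says.** All references are to the Protocol article.

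- **Primary endpoints.** "The study has two primary endpoints". On referral: "The first primary endpoint is the hospital referral rate for acute chest pain within 24 hours and 6 weeks after inclusion". On accuracy, the section relies on "the incidence of ACS and major adverse cardiac events (MACE) at the index consultation, within 6 weeks and 6 months after inclusion". That makes two referral windows and six accuracy targets (two conditions at three times). None is named as the main one.
- **Sample size calculation.** The endpoint is singular and carries no time: "For the primary endpoint, we estimated a 10% decrease in referrals, resulting in 30% referrals". One two-sided test at 0.05 with 80% power gives 448 control and 896 intervention patients, raised to 500 and 1000 for 10% loss. Accuracy has no sizing target.
- **Statistical analysis.** Referrals are compared between arms. Sensitivity, specificity, predictive values and C-statistics are calculated, with no test or threshold.
- **Intervention.** Patients with a low Marburg Heart Score and a low troponin are recommended watchful waiting. Discordant results lead to cardiologist consultation, and the GP or consulting cardiologist may overrule the rule.
- **Final diagnosis.** Diagnosis rests on GP records including hospital letters. A committee blinded to randomisation and hs-cTnI reviews all cases. The section says "we will use a delayed reference standard, defined as ACS and MACE at the index consultation", together with 6 weeks and 6 months.
- **Abstract, Methods and analysis.** The primary endpoints are "the number of hospital referrals and the diagnostic accuracy of the decision rule 24 hours, 6 weeks and 6 months after inclusion".

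**The concern.** The two referral windows can disagree. Someone sent home under the rule may be referred after a day or a week, so a reduction seen at 24 hours may have shrunk by 6 weeks. The article does not say what is concluded then. If one positive window is enough, the false-positive risk exceeds 5%. If both are needed, power is below the stated 80%. A reader also cannot tell which window the 80% refers to. Which time point is primary is part of the endpoint definition, so this is more than a detail left to an analysis plan.

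Accuracy raises a different issue. With six estimates and no lead, the most favourable can be put forward. The index-consultation version is also the most exposed to uneven verification: patients the rule clears are steered away from immediate hospital work-up, and a committee cannot adjudicate tests that were never done. Sensitivity and negative predictive value are the measures named for this endpoint, so an error towards optimism is an error in the unsafe direction.

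**Working it through.** **1. The plan's own figure.** Inputs from Sample size calculation: 40% and 30%, two-sided 0.05, 80% power, 1:2 allocation, ICC 0.05.

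With pooled proportion (0.40 + 2 × 0.30)/3 = 0.333, the unclustered control-group size is

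n = [1.96 × √(0.333 × 0.667 × 1.5) + 0.842 × √(0.40 × 0.60 + 0.30 × 0.70/2)]² / 0.10² ≈ 265, with 530 in the intervention group.

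Reaching 448 needs a design effect of 448/265 = 1.69. From 1 + (m − 1) × 0.05 = 1.69, m is about 14.8 patients per practice. The cluster size is not stated, so 448 is consistent with the inputs but cannot be confirmed. The loss step does reproduce: 448/0.9 = 498 and 896/0.9 = 996, rounded to 500 and 1000. All of this spends the full 0.05 on one comparison.

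**2. Two referral windows.** Referral within 24 hours is contained in referral within 6 weeks. For nested events with probabilities pA ≤ pB, the correlation is

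ρ = √[pA(1 − pB) / (pB(1 − pA))].

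The article gives no rate by window. I assume pA = 0.40 at 24 hours and pB = 0.42 to 0.55 at 6 weeks. I treat the two test statistics as bivariate normal with correlation ρ, so any effect of clustering on ρ is ignored. Joint power assumes each window alone has 80%.

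| 6-week rate | ρ | Type I error if either may win | Power if both required |
|---|---|---|---|
| 42% | 0.96 | 6.3% | 77% |
| 45% | 0.90 | 7.0% | 75% |
| 50% | 0.82 | 7.7% | 73% |
| 55% | 0.74 | 8.2% | 72% |

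Independent windows would give 1 − 0.95² = 9.75%, but nested windows are not independent.

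**3. Cost of the alternatives.** An equal split (0.025 each) needs 320 unclustered controls. At the implied design effect that is 320 × 1.69 ≈ 541 control and 1082 intervention. After 10% loss it is about 602 and 1203, or about 1805 in all against 1500 planned. Keeping 448 and 896, power per window falls to about 72%. A fixed sequence leaves alpha and sample size unchanged.

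**4. Accuracy at the index consultation.** Let S be true sensitivity and d the share of rule-negative ACS detected at the index visit, with all rule-positive ACS detected. Apparent sensitivity is S / [S + (1 − S)d]. Purely as illustration, S = 0.90 gives 94.7% at d = 0.5, 92.3% at d = 0.75 and 90% at d = 1. The documents supply none of these inputs. If detection is equal in both groups, the bias is zero. The formula shows the direction and the condition, not the size.

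**5. First accuracy time.** The abstract has "the diagnostic accuracy of the decision rule 24 hours, 6 weeks and 6 months after inclusion"; Primary endpoints and Final diagnosis start at the index consultation. These are different definitions unless the article equates them, which it does not.

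**The case against.** Four points can be made for the plan.

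- **Success is not wholly undefined.** The referral difference, alpha, sidedness and power are stated. This stands: only the window and the combination rule are open. A detailed multiplicity procedure may well sit in a document not shown, but naming two primary windows and sizing one unnamed comparison is a defect of this text.
- **Alpha does not reach the accuracy results.** A reader might count eight primary results and quote 1 − 0.95⁸ ≈ 34%. Statistical analysis only estimates accuracy, so that figure does not apply. This stands in full; what accuracy lacks is a lead target.
- **Inflated index sensitivity is not shown.** A reader might infer that it is established. The article does not support that. All cases are adjudicated blind to hs-cTnI, only the low-score, low-troponin group is recommended watchful waiting, GPs may overrule, and later letters can reveal cases missed at first. Upward bias requires lower detection in rule-negative patients: plausible, but not quantified. The 6-week and 6-month targets are less exposed.
- **The abstract may simply be condensed.** Its three times can be read as one list across both endpoints, so it need not assert a 6-month referral window. That stands. The mismatch of 24 hours with the index consultation remains.

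**Conclusion.** The concern holds in limited form. Hospital referral is primary at two windows without a lead, an order or a combination rule, and the planned power belongs to one comparison whose window is not named. Depending on the reading, the type I error is about 6.3% to 8.2% instead of 5%, or power is about 77% to 72% instead of 80%. Both ranges rest on the assumed window-specific rates, and the second also on 80% power for each window.

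For accuracy, the supported statement is that no lead target is named and that sensitivity at the index consultation may be overestimated, by an amount that cannot be calculated from the documents. The difference between the abstract and the main text on the first accuracy time is a plain inconsistency.

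**What to change.** 1. **Referral.** Test the two windows in a fixed sequence, each at two-sided 0.05: for example 24 hours first, and 6 weeks only if the first succeeds. The sample size section attaches no time to the 40% and 30%, so the documents do not dictate the order; the sponsor should choose and justify it.
2. **Sample size calculation.** State which window the 40%, the 30% and the 80% power refer to.
3. **Accuracy.** Name one 6-week target as the lead result and report the index and 6-month versions as supporting. The choice between ACS and MACE is the sponsor's. ACS matches the rule's stated aim; 6-week MACE is already the reference for gut feeling and the HEART score under Secondary endpoints.
4. **Consistency.** Reconcile the abstract's 24 hours with the index consultation in Primary endpoints and Final diagnosis.

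The cost is wording and a registry update, made before outcomes are compared by arm. Alpha and sample size do not change. The small downside is that the second referral window is confirmatory only if the first test succeeds.
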